### Study hypotheses

The following specific research questions will be addressed:

(i)Can SV2A PET, using the novel tracer ^18^F-SynVesT-1, be approximated quantitatively by means of a simplified reference tissue model in HV and is it quantitatively comparable to ^11^C-UCB-J?(ii)Are there regional differences between SV2A PET and ^18^F-FDG PET and do the patterns remain unchanged versus HV?(iii)Can ^18^F-SynVesT-1 PET detect various forms of dementia as accurately as ^18^F-FDG PET?(iv)Does a combination of ^18^F-SynVesT-1 PET with MR-based markers of structural abnormalities and arterial spin labeling allow a better discrimination of different forms of dementia?

Based on literature and current knowledge, the following hypotheses are formulated:

(i)Healthy aging does not result in reduced synaptic density in adults up to 85 years. ^18^F-SynVesT-1 may show a better signal-to-noise ratio and at least equivalent utility for clinical applicability compared to ^11^C-UCB-J.(ii)Simplified quantification of ^18^F-SynVesT-1 PET is possible with white matter (centrum semiovale) as reference region [30, 53] or cerebellum as pseudo-reference region [42].(iii)Synaptic density and arterial spin labeling, as indirect marker of neuronal activity, are related in absolute terms in healthy agers, while regional differences are present that may affect the sensitivity of detection of pathological consequences.(iv)^18^F-SynVesT-1 PET allows accurate detection of patients with an underlying pattern specific for Alzheimer’s disease, frontotemporal dementia and Lewy Body disease, and can discriminate these neurodegenerative diseases from healthy aging and patients with cognitive impairment due to late-life psychiatric disorder.(v)^18^F-SynVesT-1 PET has non-inferior sensitivity and specificity of diagnosis in comparison to ^18^F-FDG PET.(vi)Non-invasive determination of absolute ^18^F-FDG glucose metabolism, ASL and SV2A (SUVR) allows discrimination of patients with late-life psychiatric disorder and neurocognitive disorders with highest accuracy for synaptic density imaging.(vii)Synaptic density PET is better correlated to memory and executive neurocognitive tests compared to ^18^F-FDG PET or ASL, especially in the frontal and medial temporal cortex.

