#### Sample size

Taking into account the test-retest variability for ^18^F-SynVesT-1 (5–10%) [52]; and a non-inferiority margin of 10%, assuming an α-level of 0.025 and a statistical power of 80%, the required sample size is 8 patients, of no ‘true’ difference. As sensitivity analysis, in case this difference would be 1% or 2%, sample sizes would increase to 10 and 12 per group.

Moreover, the sample size for brain receptor single-center PET studies using absolute quantification as we do in healthy subjects is typically between 10 and 20 in most literature studies. We include 40 healthy controls and 110 patients with estimated subgroups sizes of 50 amnestic mild cognitive impairment (aMCI)-AD, 20 FTD, 20 DLB and 20 patients with late-life psychiatric disorder based on our referral data.

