Statistical analyses will be performed using GraphPad Prism version 9 (GraphPad Software, La Jolla, CA). Demographic characteristics will be compared between groups using an unpaired Student t-test, unpaired Mann-Whitney U test, Fischer’s exact test or Chi-square test for trend as appropriate. Data normality will be verified by a Shapiro-Wilk test (α = 0.05). Correlation analyses will be performed by a Pearson correlation if data are normally distributed or by a Spearman correlation if data do not follow a normal distribution. Paired student’s t-tests or a non-parametric substitute will be performed in both a voxel-based and a VOI-based analysis to investigate regional differences between ^18^F-SynVesT-1 PET and ASL. Signature patterns of reduced synaptic density for different cognitive disorders will be assessed by comparing ^18^F-SynVesT-1 in patient subgroups versus HV using Student’s t-tests or Mann Whitney U-tests. To explore the diagnostic performance of ^18^F-SynVesT-1 compared to ^18^F-FDG, scans will be visually assessed by different specialists in nuclear medicine/neurologists and diagnostic accuracy (sensitivity, specificity and accuracy) as well as the interobserver agreement will be calculated. All results will be adjusted for multiple comparisons (Bonferroni) and investigated two-sided at a significance level of 0.05.

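### Non-inferior sensitivity and specificity are hypothesised and a margin is planned, but the stated analysis has no margin-based rule and puts every result under Bonferroni, which the planning alpha does not allow for

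*Protocol article*

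**What the plan says.** The Discussion part of the abstract names the comparison of diagnostic accuracy between the two tracers as the main endpoint. Three sections bear on how it is to be judged.

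- **Study hypotheses, (v):** SynVesT-1 "PET has non-inferior sensitivity and specificity of diagnosis in comparison to" FDG PET. Two measures are named, and no margin is given on their scale.
- **Sample size:** the calculation opens with "Taking into account the test-retest variability for ^18^F-SynVesT-1 (5–10" per cent), then continues "and a non-inferiority margin of 10%, assuming an α-level of 0.025 and a statistical power of 80" per cent. It arrives at 8 patients with no true difference, and 10 and 12 per group for true differences of 1% and 2%. Neither the sidedness of the 0.025 nor any correction for multiple comparisons is mentioned.
- **Data analysis and statistics:** the accuracy comparison is introduced with "To explore the diagnostic performance of" SynVesT-1 against FDG. Sensitivity, specificity, accuracy and interobserver agreement are to be calculated. The section closes with "All results will be adjusted for multiple comparisons (Bonferroni) and investigated two-sided at a significance level of 0.05". The margin does not reappear, and the accuracy comparison is not exempted.

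**The concern.** A non-inferiority claim needs a margin and a rule that compares a confidence limit with it. The analysis section has neither. The inferential methods it does name are difference tests and correlations. If the main comparison were handled in the same way, a non-significant result would say little, since a small or noisy sample also gives one. Bonferroni would make non-significance more frequent still.

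If the closing rule is instead applied to non-inferiority bounds, Bonferroni takes the test below the alpha used in planning, and power on the main question falls below the level planned. Either way, the planning and the analysis do not describe the same test.

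**Working it through.** **1. The plan's own figure.** Inputs from the Sample size section: margin 10, alpha 0.025, power 80%, true difference d = 0, 1 or 2. The SD is given only as a range of 5–10, so a value inside it has to be assumed. Reading 0.025 as one-sided, the two-group normal approximation is

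n = 2 × [SD × (1.960 + 0.842) / (10 − d)]².

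With SD = 7 this gives 7.69, 9.50 and 12.02, so 8, 10 and 13 after rounding up. A noncentral-t calculation with SD = 6.5 gives exactly 8, 10 and 12. The stated figures therefore fit one-sided 0.025 with no multiplicity correction. They do not prove it: one-sided 0.05 with SD = 8 gives 8, 10 and 13.

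**2. Two-sided 0.05 against 0.025.** z(1 − 0.025) = 1.960 and z(1 − 0.05/2) = 1.960. The lower limit of a two-sided 95% interval is a one-sided 0.025 test, so for a single comparison the two levels agree.

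**3. What Bonferroni does.** With k comparisons the one-sided level is 0.025/k. The required n is multiplied by [(z(1 − 0.025/k) + 0.842) / (1.960 + 0.842)]². The article does not state k. Hypothesis (v) names two measures and the analysis section names three.

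| k | One-sided level | z | Factor on n | n at SD 7 (d = 0, 1, 2) | Power at n = 8, SD 7, d = 0 |
|---|---|---|---|---|---|
| 1 | 0.025 | 1.960 | 1.00 | 8, 10, 13 | 81.5% |
| 2 | 0.0125 | 2.241 | 1.21 | 10, 12, 15 | 73.1% |
| 3 | 0.0083 | 2.394 | 1.33 | 11, 13, 17 | 67.8% |

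**4. Why a non-significant difference is not enough (illustration).** Assume that SynVesT-1 is truly 10 points worse and that 110 patients are read with both tracers. The article gives no discordance, so a range is used. For discordance ψ, FDG alone is correct with probability (ψ + 0.10)/2 and SynVesT-1 alone with probability (ψ − 0.10)/2. At ψ = 0.25 these are 0.175 and 0.075. Exact two-sided McNemar at 0.05 is non-significant in:

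- 25% of trials at ψ = 0.15
- 52% at ψ = 0.25
- 63% at ψ = 0.35

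If 10 points were the margin, a non-inferiority bound would wrongly pass about 2.5% of such trials.

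**5. Power of a margin-based rule.** For a paired proportion with no true difference, power is approximately Φ(0.10/√(ψ/n) − 1.960). The 10-point margin and ψ = 0.25 are both assumptions.

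- Pooled correct classification, n = 110: √(0.25/110) = 0.0477; 0.10/0.0477 = 2.098; Φ(0.138) = 55%.
- For 80% power: 0.25 × (1.960 + 0.842)²/0.01 = 196.2, about 196 patients.
- Sensitivity and specificity each rest on only part of the 110, so power for either alone is lower. If the target were any neurodegenerative disease, the planned subgroups would give 50 + 20 + 20 = 90 for sensitivity and 20 for specificity, with power of about 47% and 14%.

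**The case against.** Four readings go further than the article supports.

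- **That two-sided 0.05 contradicts an alpha of 0.025.** Step 2 shows that it does not. The Sample size section also does not call its alpha one-sided; that is the usual convention for non-inferiority, not stated text.
- **That the stated rule cannot establish non-inferiority.** A two-sided or Bonferroni-adjusted interval set against a margin can establish it, only more conservatively. What is lacking is the margin and the comparison with it.
- **That the trial will read a non-significant difference as comparable accuracy.** The article names no difference test for the accuracy measures, does not mention McNemar, and announces no such inference. Step 4 shows the risk if the gap were filled that way, and its percentages move widely with an assumed discordance.
- **That 10 points is the trial's margin for sensitivity and specificity.** The 10% stands beside test-retest variability, which belongs to a continuous uptake measure. On that scale the Bonferroni effect takes 8 patients to 10 or 11, far below the 110 planned, so the trial's own calculation does not show a loss of power on accuracy.

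The strongest general objection is that a condensed article may leave the test and interval method to an analysis plan that is not shown. That stands for the name of the test. It does not cover the closing sentence on Bonferroni, which is stated for all results without exemption and disagrees with the planning in the same article.

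**Conclusion.** The point holds in limited form. The non-inferiority hypothesis and its planning are not carried into the stated analysis, which has no margin-based rule for the main comparison and imposes a Bonferroni correction that the sample size did not allow for. Read literally, the one-sided level falls from 0.025 to 0.0125 with two measures or 0.0083 with three, and the required n rises by about 21% or 33%. Those figures assume that 0.025 is one-sided and that k is two or three.

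The 25% to 63% range is illustrative. It assumes a true 10-point deficit, n = 110 and discordance of 15% to 35%, none of which except the 110 comes from the article.

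**What to change.** In Data analysis and statistics:

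1. Judge hypothesis (v) by the lower limit of the two-sided 95% paired confidence interval for SynVesT-1 minus FDG, from the consensus read, separately for sensitivity and for specificity. A paired score interval (Tango or Newcombe) would serve.
2. State a margin for each on its own scale, with a justification, before any accuracy result is seen. The 10% from the Sample size section should not be carried over without one.
3. Require both to succeed. Each is then tested at one-sided 0.025 and no Bonferroni correction is needed.
4. Limit Bonferroni to the secondary and regional analyses.
5. Drop the exploratory wording for this comparison.

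The cost is a few sentences and the work of justifying a margin; no further data are collected. The downside should be stated openly: power with 110 patients may be limited. It is about 55% for one pooled paired accuracy measure under the assumed 10-point margin and 25% discordance, and less for sensitivity or specificity alone. Requiring both to succeed cannot give more power than the weaker of the two.

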#### Data analysis and statistics

All reconstructed ^18^F-SynVesT-1 and ^11^C-UCB-J PET data will be corrected for motion artefacts using PMOD software (v4.1, PMOD Inc. Zurich, Switzerland). The frames of static acquisitions will be averaged and rigidly co-registered to the corresponding T1-weighted MRI. For partial volume correction, a region-based voxel-wise (RBV) correction, which is based on the Yang approach [71–73] will be applied as implemented in an in-house validated pipeline in Python 3.9 [74]. Data analysis will be done using volume-of-interest (VOI) analysis using FreeSurfer 6.0 or python 3.9 for anatomical parcellation and delineation of the VOIs. For voxel-based analysis, PET data will be spatially normalized to template space using a non-linear normalization as obtained by the CAT12 toolbox of statistical parametric mapping (SPM12; Welcome Trust Centre for Neuroimaging, University College London, UK) and smoothed using an isotropic Gaussian kernel with 8 mm FWHM (voxel size: 1.5 × 1.5 × 1.5 mm).

^18^F-SynVesT-1 and ^11^C-UCB-J uptake in HV will be quantified by distribution volume (V_T_) using a one-tissue compartment model as previously validated [26, 52]. For the tracer kinetic modeling of ^18^F-SynVesT-1 in HV, the centrum semiovale will be investigated as a reference region [30, 53] as well as the cerebellum as a pseudo-reference region [42]. For ^18^F-SynVesT-1 patient data, standardized uptake value ratios (SUVR) will be calculated after this reference region exploration in HV.

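### Bonferroni on all results, as written, also covers the smoothed voxel-based maps, where it is stricter than the stated 5%; it should be limited to VOI and endpoint families (minor)

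*Protocol article*

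**What the plan says.** All of the following is in the protocol article.

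- **Correction and level (Data analysis and statistics).** "All results will be adjusted for multiple comparisons (Bonferroni", and results are "investigated two-sided at a significance level of 0.05". No exception is made, and neither the family nor the number of tests is given.
- **Voxel-based testing (same paragraph).** Paired t-tests, or a non-parametric substitute, "will be performed in both a voxel-based and a VOI-based analysis to investigate regional differences between" SynVesT-1 and ASL.
- **Disease signatures (same paragraph).** These come from comparing SynVesT-1 "in patient subgroups versus HV using" Student's t or Mann-Whitney tests. The sentence does not say whether the tests are by voxel or by VOI.
- **Image preparation (same section, earlier).** For voxel-based analysis, images are "smoothed using an isotropic Gaussian kernel with 8 mm FWHM (voxel size: 1.5 × 1.5 × 1.5 mm").
- **Software.** "Statistical analyses will be performed using GraphPad Prism version 9". SPM12 is named for spatial normalisation and for the structural MR analyses.
- **Group sizes (Sample size).** "We include 40 healthy controls and 110 patients", the patients being estimated as 50 aMCI-AD, "20 FTD, 20 DLB and 20 patients with late-life psychiatric disorder based on our referral data".

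**The concern.** Bonferroni divides alpha by the number of tests and makes no use of the correlation between them. That suits a short list of VOIs. In a map smoothed over about five voxels in each direction, the voxel count far exceeds the number of effectively independent tests, so the threshold is higher than 5% family-wise control requires.

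The maps at risk are those for the SynVesT-1 versus ASL comparison and, if they are made voxel by voxel, the disease signatures in FTD, DLB and late-life psychiatric disorder. How synaptic density is altered in each disorder is a secondary objective. The Background section reports neocortical SV2A changes in AD of only about 10%, so moderate effects matter here. An empty map could be misread as preserved synaptic density.

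**Working it through.** **The plan's own figure.** The article gives no voxel count, mask, or power for any voxel-wise test. Its one calculation (Sample size: 8, 10 and 12) concerns non-inferiority. It is reproduced by n = (SD × (1.960 + 0.842) / (margin − difference))² with SD 10% and margin 10%, which gives 7.85, 9.69 and 12.26. It makes no allowance for multiplicity and does not bear on the maps.

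**Inputs.** From the article: 1.5 mm voxels, 8 mm FWHM, two-sided 0.05, 20 patients, 40 HV. Assumed: a search volume of 1.35 L (whole brain) or 600 mL (grey matter), effective smoothness of 8 to 12 mm, and standardised effects d of 1.0 to 2.0, because no between-subject SD is given.

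**Step 1, number of tests.** Voxel volume is 1.5³ = 3.375 mm³. Whole brain: 1,350,000 / 3.375 = 400,000 voxels. Grey matter: 600,000 / 3.375 ≈ 178,000. Resolution elements at 8 mm in the whole brain: 1,350,000 / 8³ ≈ 2,640.

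**Step 2, thresholds for 20 versus 40 (df 58).** Bonferroni is the two-sided t quantile at 0.05/m. The random-field threshold is the t at which the expected Euler characteristic of a 3D t-field equals 0.025 per tail, with the search region taken as a sphere.

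**Step 3, power at one voxel.** Noncentral t with noncentrality d × √(20 × 40 / 60) = 3.65 d.

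| Search volume and method | \|t\| threshold | d = 1.0 | d = 1.5 | d = 2.0 |
|---|---|---|---|---|
| 1.35 L, Bonferroni (p < 1.25e-7) | 6.02 | 2.0% | 33% | 87.3% |
| 1.35 L, random field, 8 mm | 5.77 | 3.2% | 41% | 91.5% |
| 1.35 L, random field, 12 mm | 5.40 | 6.1% | 54% | 95.8% |
| 600 mL, Bonferroni (p < 2.8e-7) | 5.81 | 3.0% | 39% | 90.9% |
| 600 mL, random field, 8 mm | 5.52 | 5.0% | 49% | 94.6% |

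At 8 mm the loss at d = 1.5 is 8 points in the whole brain and 10 in grey matter. At d = 1.0 or 2.0 it is 1 to 4 points. The whole-brain effect detectable with 80% power is 1.91 under Bonferroni and 1.83 under random-field control at 8 mm. A real grey-matter mask has more surface than a sphere, so its random-field threshold would be somewhat higher than 5.52 and the gain somewhat smaller.

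**Step 4, check by simulation.** In 207 null data sets (74³ = 405,224 voxels, 8 mm smoothing, 20 versus 40), the 95th percentile of the maximum |t| was 5.72, and 1.9% exceeded 5.96. Family-wise error under Bonferroni (6.02) is therefore about 2% or less, not 5%. With so few runs the figure is imprecise.

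**Step 5, the paired tests, where voxel-wise testing is explicit.** Whole-brain Bonferroni against random field at 8 mm: 6.44 versus 6.21 at n = 40 and 8.16 versus 8.19 at n = 20. The paired n is not stated.

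**Step 6, the non-parametric substitute.** The smallest two-sided Wilcoxon signed-rank p with n pairs is 2/2ⁿ. For n = 20 this is 1.9e-6, above both 1.25e-7 and 2.8e-7, so no effect of any size could pass. For n = 40 it is 1.8e-12, and the limit disappears.

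**The case against.** The case on the other side is substantial.

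- **Bonferroni is valid.** It errs towards caution and produces no excess of false claims. This stands.
- **The sentence may have been meant for VOI and tabular results.** The paragraph opens by naming GraphPad Prism, while SPM12 appears elsewhere. This is plausible, but the words cover everything, and voxel-based tests stand a few lines above.
- **Voxel-wise subgroup maps are inferred.** The article provides for voxel-based analysis in general but names it in the statistics paragraph only for SynVesT-1 versus ASL. This stands, and there the parametric loss is small or nil.
- **Most of the power drop is not due to Bonferroni.** Without correction, d = 0.78 would be detectable with 80% power. Going from 0.78 to 1.83 is the price of any whole-brain voxel-level control, and only 1.83 to 1.91 is the price of ignoring smoothness at 8 mm. This stands.
- **Masks, families and peak or cluster inference are details that an article leaves to the full protocol or SAP.** This is true of those details, and their absence is not the point. The point is the stated method and its stated scope.

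A reader might infer that the plan discards much of its power in subgroups of 20 by correcting for about 400,000 voxels. The documents do not support that. The voxel count is a whole-brain assumption, and a grey-matter mask more than halves it. Such a mask also helps Bonferroni, so a masked random-field threshold must not be set against an unmasked Bonferroni one. The 54% figure needs 12 mm effective smoothness, whereas the article documents only the 8 mm kernel.

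**Conclusion.** The point holds as a minor one. As written, a single correction covers both VOI lists and smoothed voxel maps, and for the maps it is stricter than the 5% the plan sets. For 20 versus 40 at the stated smoothing, the loss is about 8 to 10 points of power at d = 1.5 and a few points at most at d = 1.0 or 2.0. It could reach 21 points (33% against 54%) in the whole brain if effective smoothness is 12 mm. Parametric paired tests lose little or nothing. The signed-rank substitute on 20 pairs is the one place where the rule makes a positive result impossible.

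These sizes rest on assumed search volumes, smoothness and effects, and on reading the subgroup comparisons as voxel-wise. A secondary objective is touched. The main endpoint, diagnostic accuracy from visual reads against the consensus clinical diagnosis, does not depend on voxel thresholds, and the planned VOI analysis would still give evidence where a map is empty.

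**What to change.** Replace the sentence on adjustment with two rules.

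1. **VOI and endpoint analyses.** Use Bonferroni or Holm within defined families, such as a short prespecified VOI list per research question.
2. **Voxel-based maps.** Use permutation or random-field voxel-level family-wise control at two-sided 0.05, within a prespecified grey-matter mask. Prefer permutation for paired comparisons in small groups, where random-field control gains nothing over Bonferroni, and use it in place of a voxel-wise signed-rank test.

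Also state whether the subgroup versus HV comparisons are made by voxel, by VOI or both, and name SPM12 rather than GraphPad Prism as the software for the voxel-based tests.

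The cost is wording only. No extra data or patients are needed, and SPM12 is already in the plan. Make the change before any patient maps are analysed.

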## Discussion

This study will compare the diagnostic accuracy of ^18^F-SynVesT-1 to ^18^F-FDG PET in cognitive disorders with uncertain etiology and in exclusion of a neurodegenerative cause in patients with cognitive impairment in late-life psychiatric disorders. The acquisition of PET and MR imaging data as well as neuropsychological testing both in patients and HV will enable us to assess not only the relationship between cognition and imaging data but also between these different imaging modalities (PET and ASL) themselves.

Using ^11^C-UCB-J, synaptic density has been assessed in AD, FTD and DLB, compared to HV. For AD, largest effect sizes are found in the hippocampus and other medial temporal regions extending into the posterior cingulate cortex and to a lesser extent in neocortical regions [36], whereas in this population, ^18^F-FDG showed larger effect sizes especially in neocortical regions [38]. In patients with DLB, synaptic loss was observed in substantia nigra, occipital, parietal and frontal cortices but not in medial temporal regions such as hippocampus and amygdala [48]. In a direct comparison of ^11^C-UCB-J and ^18^F-FDG in DLB patients, the magnitude as well as spatial extent of hypometabolism exceeded that of synaptic loss [75]. As for FTD, decreased synaptic density was most prominent in frontal regions and to a somewhat lesser extent also in temporal regions, insula and anterior cingulate [44]. To the best of our knowledge, no direct comparison with FDG PET has been published in FTD. Although pilot studies discriminating AD from HV show larger effect sizes for hypometabolism compared to synaptic loss, regional changes e.g. in the hippocampus, may show increased specificity and effect size itself is not prohibitive to an equivalent or even better discrimination between the different dementia subtypes.

Since patients will be included upon referral for ^18^F-FDG PET at the UZ Leuven PET center, the sample will be highly representative for a real-life clinical setting. Another strength of our study is the use of simultaneous PET and MR imaging, which will allow us to investigate multiple modalities with limited associated burden for patients. We believe that achieving the anticipated sample size in an adequate time window is feasible due to this 1-scan study protocol in combination with the considerable extent of the local hospital memory clinic. ^18^F-SynVesT-1 PET will not only provide a cleaner marker of synaptic density, but it also obviates the need (i) for patients to be fasted at least four hours prior to tracer injection, (ii) to delay simultaneous MR scanning to avoid primary auditory cortex activation and (iii) to provide a dark environment prior to scanning to limit visual cortex activation. Furthermore, as visual stimulation has been shown not to change ^11^C-UCB-J levels in the occipital cortex [76], no influence of scanning with eyes open or closed is expected.

As for limitations and compromises made in the design of the study, some sources of bias may be present. Expert visual readers will be more experienced in reading ^18^F-FDG scans compared to ^18^F-SynVesT-1 scans. Therefore, they will be presented a normal dataset for visual inspection before patient reads. Due to clinical need and the importance of ^18^F-FDG PET in the diagnostic work-up, the ^18^F-FDG PET result will likely influence the final clinical diagnosis and might result in a bias in favor of ^18^F-FDG PET. Therefore, anonymized reads will be done also by expert nuclear medicine physicians not involved in the clinical workup.

The sample size calculation was based on observed effect sizes for ^11^C-UCB-J as ^18^F-SynVesT-1 data are not yet publicly available. However, similarity of ^11^C-UCB-J and ^18^F-SynVesT-1 in terms of distribution volume and binding potential as well as test-retest characteristics has been demonstrated [51, 52]. Accordingly, it can be expected to find similar effect sizes for ^18^F-SynVesT-1 as for ^11^C-UCB-J and we believe the anticipated sample size will result in adequate power. Another limitation will be the short acquisition protocol for the patient group and the associated simplified quantification method (SUVR), which was a trade-off between scanning a larger sample with simplified quantification or a smaller sample with full dynamic quantification. Of note, performing 90-minute dynamic acquisitions in a clinical setting is not feasible. As we aim to investigate the clinical applicability of ^18^F-SynVesT-1, the use of short static acquisitions is justified. The single-tracer nature of the study can be seen as a limitation since we cannot for example determine correlations with tau or amyloid PET imaging data. Nevertheless, ^18^F-FDG PET data will be acquired for clinical work-up in all patients (as inclusion criteria) and most patients will also receive lumbar punctions to determine cerebrospinal fluid levels of Aβ42/Aβ40 and total tau to exclude or confirm AD. Therefore, performing retrospective (sub)analyses using these data might also be possible upon study completion and ethics approval.

In conclusion, this study will provide further insight into synaptic density PET and its diagnostic applicability in a clinical routine setting.

